A major thrust in public health over the next decade will be to focus attention on identification and management of vascular risk factors. Although primary prevention is the ultimate goal, resources will need to be allocated to those who are at high risk and most likely to gain the greatest benefit. One such group is people who have experienced a NDS/TIA. The main objective of the PREVENT trial is to determine whether the timely delivery of a comprehensive program of secondary stroke prevention services and coordinated care can improve long-term vascular risk reduction for patients after NDS or TIA. The primary aim is to compare the effectiveness of a program of rehabilitative exercise and education (PREVENT) versus usual care (USUAL CARE) in reducing vascular risk factors in people who have had a NDS or TIA. Secondary aims are to compare between PREVENT and USUAL CARE groups (i) exercise capacity, walking endurance, daily physical activity, number of cigarettes smoked daily, medication adherence; (ii) fatigue, cognitive function, depression, health-related goal attainment and health-related quality of life; (iii) direct health costs incurred over a 1-year period; (iv) reduction in secondary vascular events, within the limitations in sample size and trial duration. We anticipate that, in comparison to USUAL CARE, timely delivery of PREVENT will produce clinically important and sustainable improvements in the outcome variables.

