#### Sample Size

Systolic blood pressure, the most robust predictor of secondary vascular events [14], was selected as the outcome variable for sample size calculation. Using estimates obtained from our pilot study, a sample size of 119 in each group will have 80% power to detect a difference in means of 4.9 mmHg, assuming that the common standard deviation is 13.4 using a two group t-test with a 0.05 two-sided significance level. We have allowed for an overall attrition rate of 5% [55], thus increasing the sample size to 125 per group (250 in total). The trial will not be sufficiently powered to determine the effectiveness of the PREVENT intervention in reducing recurrent TIA, stroke or cardiac events. Thus, it will be exploratory in this regard and will help inform the design of a future, more extensive trial.

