### Outcome Measurement

Given the long duration and multi-modal nature of the interventions, a range of outcome measures will be used to ensure evaluation of relevant variables that span the domains of the International Classification of Functioning [66]. The variables and measurement tools that will be employed are summarized in Table 1. These measures were selected based on the primary and secondary aims of the trial, clinical relevance, psychometric qualities, and feasibility (availability, cost and administration time). Evaluations will be conducted over a 2-day assessment period at baseline, post-intervention, six months, and 12 months by trained assessors blinded to knowledge of study hypotheses and group assignment. At each assessment the assessors will be asked to record their 'guess' as to the group assignment of each participant.

**Table 1 T1:** Outcome variables, measurement tools and assessment schedule

Variable	Measurement tool	Baseline	Post-intervention	6-month follow-up	12-month follow-up
*Primary measures*					

Blood pressure	Sphygmomanometer [67]	√	√	√	√

Waist girth	Tape measure [68]	√	√	√	√

Lipid profile*	Biochemical analysis	√	√	√	√

Fasting serum glucose	Biochemical analysis	√	√	√	√

Haemoglobin A1c	Biochemical analysis	√	√	√	√

*Secondary measures*					

Aerobic fitness	Peak VO_2 _using maximal treadmill stress test (ramp protocol)	√	√		√

Lower extremity function	Short Physical Performance Test [69]	√	√	√	√

Walking endurance	Six-Minute Walk Test [70]	√	√	√	√

Physical activity	Step Watch™accelerometers	√	√		√

	International Physical Activity Questionnaire [71]	√	√	√	√

Fatigue levels	Fatigue Assessment Scale [72]	√	√	√	√

Cognition	Montreal Cognitive Assessment [73]	√			√

Mental health	Hospital Anxiety and Depression Scale [74]	√	√	√	√

Quality of sleep	Pittsburg Sleep Quality Index [75]	√	√	√	√

Tobacco use	Self-report, using a health passport	√	√	√	√

Health care utilization	Self-report, using a health passport	√	√	√	√

Medication adherence	Self-report, using a health passport	√	√	√	√

Health-related quality of life	Medical Outcomes Study Short-form 36-item Questionnaire [76]	√	√		√

Health-related goals	Goal Attainment Scaling [77]	√	√	√	√

Secondary vascular events**	Health record abstraction	√	√	√	√

*Includes total cholesterol, high-density lipoprotein cholesterol (HDL-C), low-density lipoprotein cholesterol (LDL-C), triglycerides

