### Data management and analysis

Data collected at each site will be recorded on standardized forms and entered into a secure database using a centralized, web-based data entry system that contains quality control checks (e.g., range checks, notification of missing data). An independent Data Safety and Monitoring Board, consisting a cardiologist, neurologist and a statistician, has been set up to review mid-point results (or at any time that a serious adverse event occurs) and inform the investigators on issues of trial safety.

Descriptive statistics will be calculated for dependent and independent variables. Demographic and clinical characteristics of subjects in the experimental and control groups will be compared on admission using 2-sample t-tests (continuous data) and Chi-square analysis (nominal data). Nonparametric methods will be used when assumptions of normality are violated. Similar analyses will be used to compare characteristics of (i) patients who consent to participate versus those who do not; (ii) subjects who complete the study versus those who withdraw, in order to determine the representativeness of the sample. A mixed effects analysis of variance with repeated measures will be used to model the treatment effects for variables that are interval or ratio and conform to the assumptions of normality (i.e., BP, waist girth, total cholesterol, HDL-C, LDL-C, triglycerides, serum glucose, hemoglobin A1c, peak VO_2_, Six-Minute Walk Test, step counts). Non-parametric tests (Mann Whitney and Kruskall Wallis tests) will be used for ordinal level data (i.e., International Physical Activity Questionnaire, Fatigue Assessment Scale, Montreal Cognitive Assessment, Hospital Anxiety and Depression Scale, Pittsburg Sleep Quality Index, Goal Attainment Scaling) or where a normal data distribution is not found. To control for baseline differences between groups, variables that are significantly different at baseline will serve as covariates in the analyses. Data will be analyzed on an intention-to-treat basis. Significant omnibus effects will be probed with t-tests, using the Bonferroni correction to control for multiple comparisons. Multiple regression will be conducted where appropriate to examine relationships among variables. Software will include Access and SAS version 9.1. Alpha level will be < 0.05.

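### The stated 80% power is for a single unadjusted t-test of systolic blood pressure that the analysis section does not plan, so it is not shown for the planned analysis

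*Protocol article*

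**What the plan says.** The Sample Size section of the protocol article takes SBP, which "was selected as the outcome variable for sample size calculation". Its power statement is that "a sample size of 119 in each group will have 80% power to detect a difference in means of 4.9 mmHg". The SD is put at 13.4 in both groups. The test behind the figure is described in these words: "using a two group t-test with a 0.05 two-sided significance level". The section names no visit. It does not say whether 13.4 is the SD of a visit value or of a change from baseline.

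Under Outcome Measurement, "Evaluations will be conducted over a 2-day assessment period at baseline, post-intervention, six months, and 12 months". Table 1 lists blood pressure at all four times and singles out none.

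Under Data management and analysis, blood pressure is among the variables to be modelled by a mixed effects analysis of variance with repeated measures, with alpha at 0.05. The follow-up step is: "Significant omnibus effects will be probed with t-tests, using the Bonferroni correction to control for multiple comparisons". The number of comparisons is not given, nor is the omnibus term (group, or group by visit) that carries the treatment question. Covariates are to be those variables that differ significantly between groups at baseline.

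The main objective, at the end of the Background, is to learn whether the program can "improve long-term vascular risk reduction for patients after NDS or TIA".

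**The concern.** A power statement is useful only if it describes the test that will decide the question. Here the two sections describe different tests. The sizing rests on one comparison of two means at the full 0.05. The analysis reaches a comparison of two means at a visit only in two steps: an omnibus effect must be significant, and the visit t-test must then pass at a reduced level. Nowhere does the analysis section plan a single unadjusted two-group t-test of SBP.

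The 4.9 mmHg in the sample-size statement is a between-group difference in means. A significant group-by-visit effect says that the groups' courses differ. It does not by itself say how large the difference is or at which visit it lies. The long-term objective is most directly answered by a late between-group contrast, and the plan reaches that contrast through the gated, corrected step. A true effect of the size the trial was built to find could therefore be missed at the visit of interest more often than the stated 20%.

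**Working it through.** **Inputs from the documents.** 119 per group; difference 4.9 mmHg; SD 13.4; two-sided 0.05; baseline plus three later visits.

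**Inputs assumed, because the documents do not give them.** Bonferroni family size k (3 for the post-baseline visits, range 2 to 6); within-person correlation ρ of 0.3, 0.5 or 0.7, equal between all visits (compound symmetry); 13.4 taken as the SD of a visit value; no missing data.

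**1. The plan's own figure.** Standard error = 13.4 × √(2/119) = 1.737. Noncentrality = 4.9/1.737 = 2.821. With 236 degrees of freedom the critical value is 1.970, and noncentral-t power is 80.2%. The stated 80% is reproduced.

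**2. A visit t-test at the Bonferroni level.** The noncentrality is the same; the critical value is taken at 0.05/k.

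| k | level | critical t | power at one given visit |
|---|---|---|---|
| 1 | 0.0500 | 1.970 | 80.2% |
| 2 | 0.0250 | 2.256 | 71.4% |
| 3 | 0.0167 | 2.411 | 65.9% |
| 4 | 0.0125 | 2.517 | 62.0% |
| 6 | 0.0083 | 2.661 | 56.4% |

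These are the figures without the gate. Requiring a significant omnibus effect first can remove rejections but cannot add any, so the gated power at a given visit cannot exceed them.

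**3. The omnibus test alone.** Take 4.9 mmHg sustained at all three post-baseline visits and no difference at baseline. The visit differences (0, 4.9, 4.9, 4.9) have mean 3.675, and their squared deviations sum to 3.675² + 3 × 1.225² = 18.01. Noncentrality = (119/2) × 18.01 / [13.4² × (1 − ρ)], which is 8.52, 11.93 or 19.89 for ρ of 0.3, 0.5 or 0.7. With 3 and 708 degrees of freedom at 0.05, group-by-visit power is 68%, 84% or 97%. If the group main effect over all four times (baseline included) is the omnibus term instead, power is 86%, 76% or 67%. The two terms move in opposite directions as ρ rises, and each crosses 80% within the range.

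**4. Gate and t-test together.** Simulation with 6,000 runs per setting, group-by-visit gate, k = 3, visit-value t-tests and the same sustained effect:

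| ρ | significant at 12 months | significant at one or more visits |
|---|---|---|
| 0.3 | about 49% | about 66% |
| 0.5 | about 57% | about 75% |
| 0.7 | about 65% | about 81% |

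If the t-tests are on change from baseline, gated power at 12 months is about 47%, 65% or 90%.

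**5. One baseline-adjusted contrast at one visit, two-sided 0.05, no gate.** Residual SD = 13.4 × √(1 − ρ²) = 12.78, 11.60 or 9.57. Noncentrality = 4.9 / [residual SD × √(2/119)] = 2.957, 3.257 or 3.950. Power is 84%, 90% or 98%.

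**The case against.** The strongest reply is that a mismatch does not prove a shortfall. A reader might infer that the trial simply lacks its stated power, or that its power is roughly 50 to 65%. The documents support neither. The omnibus test runs at the full 0.05, and a repeated-measures model uses the within-person correlation. For a sustained effect the group-by-visit test exceeds 80% once ρ is above about 0.45. The figures of about 49% to 65% apply only to the 12-month visit, which the plan does not single out. They also require visit-value t-tests, a family of three and compound symmetry. Detection at one or more visits reaches about 81% at ρ = 0.7. All of this stands.

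A reader might also infer that the follow-up t-tests use observed cases only and ignore baseline SBP. The analysis section does not say so; they could be contrasts from the fitted model. This matters to the numbers: a baseline-adjusted contrast corrected over three visits, without the gate, has 71%, 80% or 94% power. Part of the gap between steps 2 and 5 therefore reflects baseline adjustment and not the correction.

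Lastly, the Bonferroni family, the contrast definition and the primary visit are details that a condensed article may leave to a fuller document. Their absence is not the point here. The point is that two statements in the article describe different tests, and supplying those details would not make the Sample Size statement describe the analysis in its present form.

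**Conclusion.** The point holds in a limited form. The 80% is computed correctly, but for a test that the analysis section does not plan, so it is not shown for the planned analysis. For a Bonferroni-corrected t-test of visit values, power to detect 4.9 mmHg at a given visit with 119 per group is below 80% for any family larger than one: 71%, 66% or 62% for 2, 3 or 4 comparisons. The omnibus gate can only reduce this. Whether the omnibus test itself has more or less than 80% cannot be settled from the article, because it depends on the correlation, the course of the effect over time and the term tested.

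The visit-level figures assume the family size and read 13.4 as the SD of a visit value. If 13.4 is the SD of a change, the figures in steps 3 to 5 shift.

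**What to change.** Make one between-group SBP contrast at one named visit the decisive test. Twelve months fits the long-term objective. Estimate it from the mixed model already planned, with baseline SBP as a covariate whether or not the groups differ significantly at baseline, and test it at two-sided 0.05 without the omnibus gate. Report the other visits from the same model as secondary. Tie the Sample Size statement to this contrast, giving the correlation as an assumption and saying what the SD of 13.4 refers to. With 13.4 per visit, the existing sample size gives the power in step 5 of the working.

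If the omnibus-then-Bonferroni route is kept, restate the power for that procedure, naming the omnibus term and giving the family size and the correlation as assumptions. No single replacement figure should be quoted without them.

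The cost is a change of wording in two sections, made while the trial is still enrolling. It needs no new patients or measurements. The downside is that the post-intervention and 6-month comparisons become secondary.

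### Holm's step-down procedure would hold the same familywise error as the planned Bonferroni correction for the follow-up t-tests and give up less visit-level power: a cheap improvement, not an error

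*Protocol article*

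**What the plan says.** All of this comes from the Protocol article.

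- **Data management and analysis.** For interval and ratio outcomes, "A mixed effects analysis of variance with repeated measures will be used to model the treatment effects". Then: "Significant omnibus effects will be probed with t-tests, using the Bonferroni correction to control for multiple comparisons". The section closes with "Alpha level will be < 0.05". No step-down variant is named, so ordinary single-step Bonferroni is the fair reading. The article does not say which t-tests follow or how many there are.
- **Outcome Measurement.** "Evaluations will be conducted over a 2-day assessment period at baseline, post-intervention, six months, and 12 months". By Table 1, every primary measure has three post-baseline visits. Peak VO2 and the step accelerometer have two (no 6-month visit).
- **Background.** The investigators expect that "timely delivery of PREVENT will produce clinically important and sustainable improvements in the outcome variables".
- **Sample Size.** For systolic blood pressure, "a sample size of 119 in each group will have 80% power to detect a difference in means of 4.9 mmHg". Behind this figure stand an SD of 13.4 mmHg and a single two-sided t-test at 0.05, so it is one unadjusted comparison.

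**The concern.** Single-step Bonferroni divides alpha by the number of tests and holds every test to that threshold, even after another test in the family has been declared significant. Holm relaxes the threshold after each rejection: with three tests, the smallest p-value is compared with 0.05/3, the next with 0.05/2 and the last with 0.05. Familywise error control is the same and does not depend on how the tests are correlated.

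The two procedures differ most when several comparisons in the family are truly non-null. A lasting benefit, which the investigators anticipate, would produce that situation if the follow-up t-tests compare the arms visit by visit. A real effect at 12 months could then be left unproven at visit level although the same data would have shown it under Holm.

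**Working it through.** **Inputs from the article.** Difference 4.9 mmHg, SD 13.4 mmHg, 119 per arm, two-sided alpha 0.05.

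**Inputs assumed, because the article does not give them.** A family of k = 3 between-arm tests, one per post-baseline visit; equal between-visit correlation of 0.4, 0.6 or 0.8; the same SD at each visit; 119 per arm at each visit. The omnibus gate is not modelled.

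**1. Reproduce the plan's figure.** Noncentrality = 4.9 / (13.4 × √(2/119)) = 2.82 on 2 × 119 − 2 = 236 degrees of freedom. The noncentral t distribution gives 80.2% power at alpha 0.05, which agrees with the stated 80%.

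**2. Power of one t-test at each threshold Holm uses.**

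- 0.05/3 = 0.0167: 65.9%
- 0.05/2 = 0.025: 71.4%
- 0.05: 80.2%

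Bonferroni holds every visit to the first line. Holm moves down the list as tests are rejected.

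**3. Simulate both procedures.** I drew 200,000 sets of three correlated t-statistics per setting and applied both procedures to the same p-values. Each cell gives Bonferroni v Holm.

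| Quantity | corr. 0.4 | corr. 0.6 | corr. 0.8 |
|---|---|---|---|
| 4.9 mmHg at all visits: 12-month test | 66% v 74% | 66% v 73% | 66% v 72% |
| 4.9 mmHg at all visits: all three significant | 39% v 57% | 45% v 61% | 51% v 66% |
| 4.9 mmHg at all visits: at least one significant | 89% v 89% | 85% v 85% | 80% v 80% |
| Fading 4.9, 3.7, 2.45 mmHg: 12-month test | 16% v 24% | 16% v 25% | 16% v 26% |
| Effect at 12 months only: 12-month test | 66% v 66% | 66% v 66% | 66% v 66% |
| No effect: any false positive | 4.6% v 4.6% | 4.2% v 4.2% | 3.5% v 3.5% |

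Holm rejected everything Bonferroni rejected in every simulated data set. The first step of both procedures is the same test, so the chance of at least one rejection is identical.

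**4. What the repeated-measures model can do without the correction.** Suppose the group effect averages the three post-baseline visits. The variance of that average is (1 + 2ρ)/3 times the single-visit variance, so the noncentrality is 2.82/√((1 + 2ρ)/3): 3.64, 3.29 and 3.03 at ρ = 0.4, 0.6 and 0.8. With 4.9 mmHg at every visit, power at alpha 0.05 is about 95%, 91% and 85%.

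**The case against.** **Bonferroni is a valid choice.** It is pre-specified and conservative, inflates no error rate and contradicts nothing else in the article. This stands in full. A reader might infer a mistake in the analysis plan; the article does not support that.

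**The family is not stated.** The t-tests could be between-arm at three visits, between-arm at four, or within-arm changes over time. This stands, and an article may leave it to the full protocol. The 0.05/3 threshold is therefore an assumption, and so is the size of the loss. The direction is not: Holm never rejects less, whatever the family.

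**A sustained effect does not have to be shown visit by visit.** A reader might infer that the trial must reach significance at several visits to claim lasting benefit. The article anticipates sustained improvement but sets no such rule. If a claim did require every visit to be significant, each test could be run at 0.05 for that joint claim with no correction at all. The all-three figures therefore illustrate the difference between procedures; they are not the power of a planned claim.

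**The t-tests are only probes.** They follow a significant omnibus effect in a model that can itself show a lasting group effect with high power (step 4). This stands: power for a sustained effect is not lost overall. But an effect averaged over visits does not establish that benefit is still present at 12 months. If the t-tests are between-arm by visit, that statement comes from them.

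**Bonferroni buys something.** It gives simple simultaneous confidence intervals that agree with the tests, and Holm does not readily do so. This stands, so it would be wrong to say the power is given up for nothing. The article does not say whether such intervals are planned.

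**Conclusion.** The point holds as an optional efficiency gain. At the same familywise error and with no added assumptions, Holm is never less powerful than the named correction.

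With three between-arm tests, a constant 4.9 mmHg effect and correlation 0.4 to 0.8, the gain is about 7 to 8 percentage points at 12 months and 15 to 18 points for all three visits. With the fading pattern it is about 8 to 10 points at 12 months. It is about nil when a single visit carries the effect, and exactly nil for the first rejection. All of these sizes rest on the assumed family and correlation.

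A reader might also infer that the stated 80% power is wrong or that more patients are needed. Neither follows: the sample size is for one unadjusted t-test and reproduces, and neither it nor the omnibus test is touched by this choice.

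**What to change.** In Data management and analysis, replace the reference to the Bonferroni correction with Holm's step-down Bonferroni procedure, applied to the family of follow-up t-tests. State that family, for example the between-arm comparisons at the post-baseline visits: three for the primary measures, two for peak VO2 and step counts.

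The cost is one sentence, with no new data or patients. The article lists the trial as still enrolling, so the change can be made before the final analysis.

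The downside is in the intervals. Simultaneous confidence intervals that match Holm are less simple. If unadjusted 95% intervals are shown beside Holm-adjusted p-values, they may occasionally disagree (an interval excluding zero with an adjusted p-value above 0.05), so they should be labelled as unadjusted. If simple matching intervals matter more to the investigators than the extra power, keeping Bonferroni is defensible.

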## Discussion

The main focus of PREVENT Trial is to investigate the role of aerobic exercise, education and lifestyle counselling in reducing vascular risk factors of people after TIA or NDS. This trial will contribute much needed evidence to begin answering important clinical questions regarding the role of non-pharmacological interventions, modelled after cardiac rehabilitation programs, in preventing second stroke in the often under-served patient populations involved in this trial. Although the trial is not sufficiently powered to determine the effectiveness of PREVENT on hard clinical outcomes such as second vascular events or death, we will compare occurrence rates between groups in order to inform future, larger scale trials.

This multi-site RCT will also explore the impact of the PREVENT program on cardiovascular fitness, walking tolerance, fatigue, cognition, mental health, quality of sleep, medication adherence, tobacco use, and health-related quality of life, which may be mitigating factors in reducing vascular risk factors, and, ultimately, stroke recurrence. As well, comparison of the direct health costs of the PREVENT and USUAL CARE groups over the course of the study will provide important preliminary information related to cost effectiveness and sustainability of multi-modal, behavioral interventions such as PREVENT.

